**6.0.1 Lumbar puncture**

Subjects will be placed on their side with knees drawn upwards and lumbar spinal space L2-3 or L3-4 will be located; whereupon the back will be cleaned with surgical antiseptic and a local anesthesia will be injected to numb the insertion area.

A 22 gauge spinal needle will be used to obtain lumbar CSF. Approximately 15 mL of CSF will be obtained for RGV assays.

NOTE: See Appendix for CSF sample processing instructions.

**6.0.2. Serial blood collection by indwelling catheter**

An indwelling venous catheter will be placed for pharmacokinetic sampling in a peripheral arm vein.

Blood samples will be collected at intervals through a saline lock (or occasionally by venipuncture if the saline lock does not allow blood to be drawn).

Each blood sample will be promptly placed on wet ice until refrigerated.

For plasma PK, samples will then be centrifuged at 4OC at 800xg for 10 minutes within one hour of collection.

Plasma will be harvested from the collection tube and 4 aliquots of each will be transferred into pre-labeled tubes and stored frozen at ‑70OC.

For PBMCs, whole blood samples will immediately be placed in a wet ice bath, and processed as described in Appendix C.

**6.0.3 Adherence assessment**

An adequate supply of study medication will be dispensed to last for 7 days (14 pills). All unused pills should be returned to study personnel. At the Day 6 or 7 visit (before PK sampling) study personnel will perform pill counts.

Daily medication logs, completed by each subject, and pill counts will be used for adherence monitoring. On Days 1, 2, or 3 subjects may miss NO MORE THAN ONE DOSE of study drug. On Days 4, 5, and 6 subjects MUST NOT MISS ANY DOSE of study drug.

Any subject who fails to meet these criteria will discontinue study medication. The subject will be taken off study.

**6.0.4 Summary of study events by day**

"Day 1" is the day that study drug is first administered.

Days -365 to -1

1. Obtain written informed consent

2. Venipuncture to obtain blood sample for *ABCB1* genotype.

NOTE: The -365 day window is intended to allow flexibility so that *ABCB1* genotype assays can be batched to increase genotyping efficiency and to accommodate subjects’ schedules. The actual time interval from consenting to Day 1 will be far less than 90 days in most participants.

Days -30 to -1

1. Venipuncture to obtain blood sample for screening safety lab tests, HIV serology.

2. History and physical examination.

3. Neurological examination.

4. Routine screening laboratory assay.

4. Urine pregnancy test (Women only. Must have negative test before taking study medications).

Day 1

1. Urine or Serum pregnancy test (Women only. Must have negative test before beginning study drug).

2. Provide participant with medication diary to document timing of every dose of RGV.

3. Begin RGV 400 mg orally every 12 hours. The first dose is at time specified by study personnel on Day 1.

Days 2-6

1. Continue RGV 400 mg orally every 12 hours in the AM and in the PM, as instructed.

Day 6

1. Arrive at VICTR-CRC in evening, at time specified.

2. Venipuncture to obtain blood sample for safety lab tests.

3. Provide snack 30min. prior to study drug administration.

4. Collect medication diary from participant, and assess adherence.

5. Continue RGV 400 mg orally every 12 hours. The scheduled PM dose of RGV 400 mg should be observed by VICTR-CRC staff and documented.

6. Leave the VICTR-CRC after taking the observed dose of RGV

NOTE: Under rare circumstances the participant may stay in the VICTR-CRC overnight on Day 6.

NOTE: Participant needs to be fasting 8 hours before the final scheduled AM dose of RGV. Only water and coffee with no cream or sugar are allowed.

Day 7

1. Arrive at VICTR-CRC at 6 AM. Admit as inpatient.

2. Day 6 lab results reviewed.

3. Fasting is required for an additional 3 hours after final dose of RVG. Water and coffee with no cream or sugar are allowed. A light regular meal will be given 3 hours after final dose of RVG.

4. Consent form re-signed for LP.

5. Place an indwelling venous catheter in a peripheral arm vein.

6. Serial plasma and PBMC sampling for RGV PK.

NOTE: See Appendix for timing and processing of plasma and PBMC samples.

7. Lumbar puncture 4 hours after the morning RGV dose.

Day 8

1. Plasma and PBMC sample for RGV PK (24 hours  1 hour after Day 7 RGV dose).
2. After sample is obtained, discharge participant from the VICTR-CRC.

Day 9

1. Plasma and PBMC sample for RGV PK (48 hours  1 hour after Day 7 RGV dose).

Day 14 (± 2 days)

1. Contact participant by telephone (or email if the participant prefers) to make sure there were no subsequent problems related to study participation.

**6.0.5 Study medications**

The following regimen will be used in this study. All doses will be administered with food (except fasting for 8 hours prior to the last dose). There will be no dosage adjustment for weight. Subjects who complete the study will receive study drug for 7 days.

Raltegravir 400 mg orally PO every 12 hours

1. **Risks**

**Potential risks associated with CSF sampling by lumbar puncture**

Lidocaine, used locally during the lumbar puncture initiation, may cause a burning sensation. Local lidocaine injection very rarely enters the bloodstream. There is a risk that lidocaine may cause cardiac arrhythmias. CSF collection may cause bruising at the site, and may result in headache following the procedure. The risks associated with lumbar puncture include most commonly mild transient backache during the procedure, and headache subsequent to the procedure. While these are usually mild to moderate in nature and go away in a day or two, they may last longer (10 days) and have been occasionally more severe (requiring a dextran patch to bring resolution.) Rare and unexpected but potentially more serious side effects from having spinal fluid withdrawn are infection, nerve root damage, and bleeding at the puncture site. The lumbar puncture may produce, on occasion, a sharp, acute, very brief (10-30 seconds) pain in the nerve distribution to the thigh muscle or groin that remits with needle removal. The risks associated with the dextran patch procedure are the same as those associated with the catheterization procedure itself and in addition some individuals will develop transient (several days) post-patch ringing in their ears and a low-grade fever. Headache may also be treated with caffeine sodium benzoate that is associated with increased alertness and jitteriness. There is a negligible risk of infection from having blood samples drawn, and some risk of bruising and discomfort at puncture sites.

Should headache occur, the subject will remain at bed rest until it is gone. Virtually all headaches related to lumbar CSF sampling are posture-related and can be ameliorated by bed rest. Hydration and analgesia will be used as well. If headache occurs before the participant is discharged from the VICTR-CRC, caffeine sodium benzoate (500mg, 2 hour IV drip) will be recommended as a primary treatment. If treatment is successful, the subject will be asked to remain for a minimum of 4 hours rest and observation on the VICTR-CRC. If the first effort at treatment is unsuccessful, 8 hours for rest and observation will be recommended before a second effort at treatment. The second recommended treatment could be a repeated injection of caffeine, or a blood or dextran patch. If headache occurs after discharge from the VICTR-CRC, and is refractory to hydration and analgesics, a blood or dextran patch will be used. The choice of blood versus dextran patch will be based on the clinical judgment of the anesthesiologist performing the procedure. The blood or dextran patch typically brings nearly instantaneous resolution of the headache. All patients will be contacted one week following lumbar puncture to obtain follow-up safety information.

**Potential side effects of study medications**

Raltegravir is very well tolerated, without apparent untoward side effects. However, there may be unknown or unanticipated adverse effects.

1. **Reporting of Adverse Events or Unanticipated Problems involving Risk to Participants or Others**

All serious adverse events or other unanticipated problems involving risk to participants or others will be reported per FDA guidelines and to the Vanderbilt IRB within 48 hours of them being identified. All Grade 3 or higher adverse events will be reported to the Vanderbilt IRB.

A serious adverse event or reaction is any untoward medical occurrence that:

- Results in death;
- Is life-threatening-

(Defined as an event in which the patient or subject was at risk of death at the time of the event; it does not refer to an event which hypothetically might have caused death if it were more severe.);

- Requires inpatient hospitalization or prolongation of existing hospitalization;
- Results in a persistent or significant disability/incapacity;
- Is a congenital anomaly or birth defect;
- Results in the development of drug dependency or drug abuse;
- Is an important medical event-

(Defined as a medical event(s) that may not be immediately life-threatening or result in death or hospitalization but, based upon appropriate medical and scientific judgment, may jeopardize the patient/subject or may require intervention (e.g., medical, surgical) to prevent one of the other serious outcomes listed in the definition above. Examples of such events include, but are not limited to, intensive treatment in an emergency room or at home for allergic bronchospasm; blood dyscrasias or convulsions that do not result in hospitalization.

Adverse events will be graded using the National Instituteof Allergy and Infectious Diseases Division of AIDS toxicityscale (http://rcc.tech-res-intl.com/tox_tables.htm). [name] holds the IND for this study. He will be made promptly aware of any SAEs that occur during the study. In addition, he is responsible for making sure that any SAEs are promptly reported to the FDA by his research staff.

1. **Study Withdrawal/Discontinuation**

Study subjects may be withdrawn from the study for any of the following reasons:

- Drug-related toxicity
- Failure to take study medications as instructed
- Clinical reasons believed life threatening by the physician
- Request by the subject to withdraw
- Request of the primary care provider if s/he thinks the study is no longer in the best interest of the subject
- Subject judged by the investigator to be at significant risk of failing to comply with the provisions of the protocol as to cause harm to self or seriously interfere with the validity of the study results
- Inability to obtain CSF for technical reasons
- Subjects who become prisoners or become involuntarily incarcerated for the treatment of either a psychiatric or physical (e.g., infectious disease) illness within the first 14 days of study participation.

1. **Statistical Considerations**

**Pharmacokinetic parameters**

The concentration of RGV in CSF and plasma will be determined by GC/MS assay. Plasma pharmacokinetic parameter estimates will be determined using a non-compartmental approach (WinNonlin version 4.01, Pharsight Corp., Mountain View, CA.). Calculated pharmacokinetic parameters will be: area-under-the-curve (AUC0-12h), maximum plasma concentration (Cmax), minimum plasma concentration (Cmin), time to Cmax (Tmax), oral clearance (CL/F), terminal apparent distribution volume (Vz/F), and elimination half-life (t1/2). AUC0-12h willbe determined using the linear/log trapezoidal method. Cmax, Tmax, and C12h will be taken directly from the observed concentration-time data. CL/F will be calculated as dose/AUC0-12h. Vz/F will be calculated as dose divided by the product of the elimination rate constant (z) and AUC0-12h. The elimination rate constant will be determined by linear regression of the terminal elimination phase concentration-time points; t1/2 will be calculated as ln(2)/z.

**Statistical analyses**

There are no data to reliably predict for RGV the ratio of CSF C4h to plasma AUC0-12h values. We expect this ratio to be quite low. Our power calculation is therefore only a rough estimate. If we assume that PK values will be normally distributed within each *ABCB1* genotype group, a standard deviation of 0.001 for the CSF-to-plasma ratio, and using Student’s t test, studying 17 individuals in each genotype group will allow us to detect with 80% power and an alpha of 0.05 a difference of 0.001 between *ABCB1* C/C and T/T genotype groups. Because we anticipate that not all participants will be evaluable, we will enroll 3 additional individuals in each of the genotype groups, for a total of 20 per genotype group.

The primary outcomes of interest will be ratios of the CSF RGV C4h value to the plasma RGV Cmax, Cmin and AUC0-12h values. If PK parameters are normally distributed within each genotype group, then genotype groups will be compared using Student’s t test. If PK parameters are not normally distributed within each genotype group, then genotype groups will be compared using nonparametric tests such as the Mann-Whitney U test.

1. **Privacy/Confidentiality Issues**

All laboratory specimens, evaluation forms, reports, and other records that leave the site will be identified by coded number only to maintain subject confidentiality. All records will be kept locked. All computer entry and networking programs will be done with coded numbers only.

1. **Follow-up and Record Retention**

Study records will be retained for at least 10 years.

**Appendix A:** Schedule of events

|  |  |  |  |  |  | Day |  |  |  |  |  |  |
| --- | --- | --- | --- | --- | --- | --- | --- | --- | --- | --- | --- | --- |
|  | Screen -365 to -1 | Screen -30 to -1 | 1 | 2 | 3 | 4 | 5 | 6 | 7 | 8 | 9 | 14 (±2) |
| **All subjects** |  |  |  |  |  |  |  |  |  |  |  |  |
| Informed consent | X |  |  |  |  |  |  |  | X |  |  |  |
| *ABCB1* genotype | X |  |  |  |  |  |  |  |  |  |  |  |
| Routine safety labs (creatinine, CBC with diff, platelet count, ALT, AST, alkaline phosphatase, bilirubin, creatinine kinase (CK)) |  | X |  |  |  |  |  | X |  |  |  |  |
| HIV serology |  | X |  |  |  |  |  |  |  |  |  |  |
| Urine or Serum pregnancy test (women only) |  | X | X |  |  |  |  |  |  |  |  |  |
| Take raltegravir 400 mg every 12 hours |  |  | X | X | X | X | X | X | X |  |  |  |
| VICTR-CRC visit (admission to VICTR-CRC in rare circumstances) |  |  |  |  |  |  |  | X | X |  |  |  |
| CSF for total protein, cell count |  |  |  |  |  |  |  |  | X |  |  |  |
| Phone/or email follow-up |  |  |  |  |  |  |  |  |  |  |  | X |
| **Clinical evaluations** |  |  |  |  |  |  |  |  |  |  |  |  |
| Complete physical exam (includes height, weight, funduscopic, neurologic exam) |  | X |  |  |  |  |  |  |  |  |  |  |
| Funduscopic, targeted neurologic exam before LP. |  |  |  |  |  |  |  |  | X |  |  |  |
| Medication adherence assessment; distribution/collection of medication log |  |  | X |  |  |  |  |  | X |  |  |  |
| **Pharmacokinetic (PK) sampling** |  |  |  |  |  |  |  |  |  |  |  |  |
| Serial plasma sampling for PK |  |  |  |  |  |  |  |  | X | X | X |  |
| PBMC sampling for PK |  |  |  |  |  |  |  |  | X | X | X |  |
| Lumbar puncture for PK 4 hours after morning RGV dose |  |  |  |  |  |  |  |  | X |  |  |  |

**Appendix B:** References

Reference List

(5) Polli JW, Jarrett JL, Studenberg SD, et al. Role of P-glycoprotein on the CNS disposition of amprenavir (141W94), an HIV protease inhibitor. Pharmaceutical Research16:1206-12.

(7) Letendre S, et al. Better Antiretroviral Penetration into the Central Nervous System Is Associated with Lower CSF Viral Load . Presented at 13th Conference on Retroviruses and Opportunistic Infections, February 2006, Denver, CO Abstract 74 2006.

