# Appendix E: Pharmacokinetic (PK) Evaluations

**SCHEMA**

**Genetic Predictors of Raltegravir Penetration into Cerebrospinal Fluid**

DESIGN: This single arm, open-label healthy volunteer study will determine whether there are associations between a frequent C>T single nucleotide polymorphism (SNP) at position 3435 (rs1045642) in the drug transporter gene *ABCB1* (also known as *MDR1*) and penetration of raltegravir (RGV) into cerebrospinal fluid (CSF). Study participants will take RGV 400 mg orally every 12 hours for 7 days. On Day 7 of RGV participants will undergo 24-hour serial plasma sampling to determine steady-state plasma pharmacokinetic (PK) parameters for RGV. A plasma sample will also be obtained on Day 9. Peripheral blood mononuclear cells (PBMCs) will be obtained to measure intracellular RGV. Lumbar puncture will be performed 4 hours after the morning dose on Day 7 to quantify the CSF RGV concentration. Primary outcomes of interest will be ratios of the CSF RGV C4h value to the plasma RGV Cmax, Cmin and AUC0-12h values.

DURATION: Subject’s participation may last as many as 12 months, but in most cases approximately 3 month.

SAMPLE SIZE: This study will enroll 40 subjects over approximately 2 year.

POPULATION: Healthy, HIV-negative volunteers who are at least 18 years of age, with body mass index less than 30, and with acceptable screening laboratories. Only individuals of self-reported white European ancestry, and whose parents’ were both of white European ancestry may participate. With regard to *ABCB1* 3435 C>T, the study will include 20 C/C homozygotes and 20 T/T homozygotes. Each genotype group will comprise 10 males and 10 females, as follows:

|  | *ABCB1* 3435 genotype | |
| --- | --- | --- |
|  | C/C | T/T |
| Male | 10 | 10 |
| Female | 10 | 10 |

RANDOMIZATION: None

REGIMEN: Study participants will receive RGV 400 mg orally every 12 hours for 7 days.

1. **Background**

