**SPECIFIC AIMS:**

2.0.1 **Primary aim**

1. To determine whether *ABCB1* 3435C>T is associated with altered cerebrospinal fluid (CSF)-to-plasma RGV concentration ratios among healthy volunteers at steady state.

2.0.2 **Secondary aims**

1. To determine whether *ABCB1* 2677G>T and/or other *ABCB1* SNPs are associated with altered CSF-to-plasma RGV concentration ratios among healthy volunteers at steady state.

2. To characterize PBMC intracellular pharmacokinetics of RGV at steady state, and associations with *ABCB1* 3435C>T and 2677G>T.

3. To characterize plasma terminal elimination pharmacokinetics of RGV, and associations with *ABCB1* 3435C>T and 2677G>T.

4. To store leftover DNA, plasma and CSF specimens that may be used for future unplanned analyses of RGV and/or its metabolites, and of additional human DNA polymorphisms.

1. **Animal Studies and Previous Human Studies**

See Investigator Brochure for Raltegravir (MK-0518).

1. **Inclusion/Exclusion Criteria**

4.0.1 **Study participants**

The study will enroll 40 healthy volunteers. Of these 40 individuals, 20 will be *ABCB1* position 3435 C/C homozygotes, and 20 will be 3435 T/T homozygotes. Each of the two genotype groups we comprise 10 males and 10 females. There will therefore be 4 separate groups.

4.0.2 **Inclusion Criteria**

1. Able and willing to give written informed consent.

2. Negative HIV-1 serology documented by any licensed ELISA test kit within 30 days prior to initiating study drug.

3. Men and women at least 18 but no more than 55 years of age at study entry.

4. Body mass index less than 30.

Body mass index = (weight in kilograms)/(height in meters)2

OR

Body mass index = [(weight in pounds)/(height in inches)2] X 703

5. Estimated creatinine clearance ≥ 50 mL/minute within 30 days prior to study entry, calculated by the Cockcroft-Gault method as follows:

Men: creatinine clearance = [(140 - age) x (weight in kg)]/(72 x serum creatinine)

Women: creatinine clearance = 0.85 x [(140 - age) x (weight in kg)]/(72 x serum creatinine)

6. Laboratory values obtained within 30 days prior to study entry:

- Absolute neutrophil count (ANC) ≥ 1,000/mm3.
- Hemoglobin  12.5 g/dL for males and  11.5 g/dL for females.
- Platelet count  100,000/mm3.
- AST (SGOT), ALT (SGPT), and total bilirubin within normal range.
- Alkaline phosphatase  1.5  upper limit of normal (ULN).

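### Three unranked ratios are primary for one aim, but the stated 17 per group, 80% power and alpha 0.05 hold together for one ratio only

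*Protocol*

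**What the plan says.** The protocol has one primary aim (Specific Aims, 2.0.1): whether *ABCB1* 3435C>T "is associated with altered cerebrospinal fluid (CSF)-to-plasma RGV concentration ratios among healthy volunteers at steady state". The word for ratios is plural and none is singled out.

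The outcomes serving that aim are listed twice. The Schema (DESIGN) has "Primary outcomes of interest will be ratios of the CSF RGV C4h value to the plasma RGV Cmax, Cmin and AUC0-12h values". Statistical Considerations, under Statistical analyses, has the same list: "The primary outcomes of interest will be ratios of the CSF RGV C4h value to the plasma RGV Cmax, Cmin and AUC0-12h values". Neither place orders the three or states a success rule.

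The sample-size paragraph in the same section opens on one ratio only: "There are no data to reliably predict for RGV the ratio of CSF C4h to plasma AUC0-12h values". It then assumes "a standard deviation of 0.001 for the CSF-to-plasma ratio, and using Student’s t test", in the singular, and concludes that "studying 17 individuals in each genotype group will allow us to detect with 80% power and an alpha of 0.05" a difference of 0.001 between the C/C and T/T groups. Three more participants per group are added for non-evaluable cases, giving 20. The protocol calls the calculation a rough estimate.

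The paragraph on the comparison itself names Student's t test, or a nonparametric test such as Mann-Whitney, and gives no significance level. The value 0.05 appears only inside the power calculation. No SD or target difference is given for the Cmax or Cmin ratio.

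**The concern.** Three tests bear on one claim, while the error rate and power are set out as if there were one test. The three ratios share a numerator but have different denominators, so they can disagree. If one ratio gives p = 0.03 and the other two give p = 0.15, the protocol does not say whether the primary aim has been met. That cannot be settled credibly once the three p-values are known.

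The number evaluable, the power and the alpha depend on the missing rule. Under each possible rule for three ratios, at least one of the protocol's stated figures has to give way.

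There is also a question of scale. C4h/AUC0-12h has units of 1/time, whereas the other two ratios are dimensionless. An SD and difference of 0.001 assumed for the first says nothing about the other two.

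**Working it through.** **Inputs from the protocol (Statistical analyses):** SD 0.001; difference 0.001; alpha 0.05 (sidedness not stated); power 80%; 17 evaluable per group; 20 enrolled per group; Student's t test; three primary ratios. **Assumed:** the correlation between the ratios, which the protocol does not give. A shared numerator makes positive correlation likely, so a range from 0 to 0.95 is shown.

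**1. Reproduce the stated figure for one ratio.** The standardised difference is d = 0.001/0.001 = 1. The t statistic has 2n − 2 degrees of freedom and noncentrality d·√(n/2). At n = 17 that is 32 degrees of freedom, noncentrality √8.5 = 2.915 and a two-sided 5% critical value of 2.037.
- n = 16: power 78.1%
- n = 17: power 80.7%
- n = 20: power 86.9%

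So 17 per group is correct for one ratio, two-sided. A one-sided test would reach 80% with 14 per group (82.4%), so the stated n implies a two-sided test.

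**2. If any one ratio at 0.05 sufficed.** Under independence the chance of at least one false positive is 1 − (1 − 0.05)³ = 1 − 0.8574 = 14.3%. The Bonferroni upper bound is 3 × 0.05 = 15%. Simulating three equally correlated normal outcomes at 17 per group gives:

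| Assumed correlation | At least one false positive |
| --- | --- |
| 0 | about 14% |
| 0.5 | about 13% |
| 0.8 | about 10% |
| 0.9 | about 8.5% |
| 0.95 | about 7% |

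**3. If alpha were split equally.** Each ratio is tested at 0.05/3 = 0.0167. At n = 17 the critical value rises to 2.526 with the same noncentrality, 2.915.
- n = 17: power 65.2% per ratio
- n = 20: power 74.2%
- n = 22: power 79.1%
- n = 23: at least 80% (81.2%)

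The 23 evaluable needed per group exceeds the 20 to be enrolled. At 17 per group, the smallest difference detectable with 80% power rises from 0.99 SD to 1.16 SD.

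**4. If all three had to be significant at 0.05.** The false-positive rate stays at or below 5%. Power, assuming a true 1-SD difference on every ratio, is 0.807³ = 52.6% at correlation 0. By simulation it is about 62% at 0.5, 73% at 0.9 and 75% at 0.95. If all 20 per group were evaluable, the range is about 66% (correlation 0) to 83% (0.95), reaching 80% only at a correlation of about 0.9 or more.

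**5. If the AUC0-12h ratio alone decides, or is tested first in a fixed order.** Power is 80.7% at two-sided 0.05 with 17 per group, as in step 1. Of the rules examined, only this one gives the protocol's three figures together.

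**6. Scale of the other ratios.** Average concentration over the interval is AUC0-12h/12, and it must lie between Cmin and Cmax. Hence C4h/Cmin ≥ 12 × (C4h/AUC0-12h), and C4h/Cmax ≤ 12 × (C4h/AUC0-12h), with AUC in concentration-hours. The ratios sit on different numerical scales, so one absolute SD and difference cannot describe all three.

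**The case against.** A reader might infer that each ratio is to be tested at 0.05, that any one success will be claimed, and that the trial therefore runs at two to three times its stated error rate. The protocol does not support that. It gives 0.05 only in the power calculation, sets no level in the comparison paragraph, makes no explicit promise of family-wise control and states no any-one rule. Requiring all three, or testing in a fixed order, would keep the error rate at or below 5%. A statistical analysis plan that is not shown could specify either. The inflation figures are therefore conditional, and their size rests on correlations nobody has measured. At high correlation the excess is modest.

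It is also fair to say that 17 per group depends only on a difference of 1 SD. It would serve any single ratio with that standardised effect, so two ratios lack a justification rather than having a wrong n. The Bonferroni figures are conservative for positively correlated outcomes. The protocol is also open that its power calculation is rough, and no treatment decision is tied to this test in 40 healthy volunteers.

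All of that stands, and it limits the point's strength. It does not remove the point. The choice of primary outcomes and the sample size are fixed in this protocol, not deferred, and they do not fit together. An analysis plan that kept three primaries would have to give up the stated power at 17 per group or the 5% level. The roughness concerns the assumed SD and effect, and does not say which ratio decides the aim.

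**Conclusion.** The point holds in this limited form. Three ratios are named primary for one aim, with no order and no success rule, while the sample size is justified for the AUC0-12h ratio only. The stated 17 per group, 80% power and alpha 0.05 are jointly correct for one ratio (80.7%).

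With three primaries at 17 per group, the cost is one of the following:
- a false-positive rate of about 7% to 14% under an any-one rule, over assumed correlations of 0.95 down to 0;
- power of 65% under an equal split;
- power of about 53% to 75% if all three are required.

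The power figures assume normal data and a 1-SD difference on each ratio tested. The documents do not establish that the 5% level is actually breached, because the decision rule that would breach it is not stated. The Cmax and Cmin ratios have no sample-size basis in the protocol. This should be fixed before the data are analysed. It affects how the primary result is read, not participant safety or the data collected.

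**What to change.** In the Schema (DESIGN) and in Statistical analyses, name CSF C4h over plasma AUC0-12h as the sole primary outcome, tested at two-sided 0.05, and list the Cmax and Cmin ratios as secondary. Put the primary aim's ratio in the singular to match. If the sponsor prefers to keep formal tests of all three, a fixed order with the AUC0-12h ratio first also preserves the stated n, power and alpha for that first test.

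The change is a sentence in each place. It needs no further participants, lumbar punctures or samples, and 17 evaluable per group stays valid under the protocol's own assumptions. The small downside is that the Cmax and Cmin ratios can no longer carry the primary claim (under a fixed order, not unless the AUC0-12h ratio is significant first). If all three must stay primary on an equal footing, the protocol needs a stated success rule, an SD and difference for each ratio, and a matching sample size. Under an equal alpha split and 1-SD differences that means 23 evaluable per group.

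### Enrolment is balanced by sex within genotype, but the primary comparison ignores sex, which gives up precision if sex affects the CSF-to-plasma ratio

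*Protocol*

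**What the plan says.** The Schema fixes the enrolment by sex: "Each genotype group will comprise 10 males and 10 females, as follows", followed by a two-by-two table with 10 in each cell. Protocol section 4.0.1 repeats the numbers and concludes "There will therefore be 4 separate groups".

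The Statistical analyses paragraph names the tests for the primary outcomes, which are "ratios of the CSF RGV C4h value to the plasma RGV Cmax, Cmin and AUC0-12h values". In the normal case, "If PK parameters are normally distributed within each genotype group, then genotype groups will be compared using" Student's t test. Otherwise, "genotype groups will be compared using nonparametric tests such as the Mann-Whitney U test". Neither the aims, the power calculation nor the analysis paragraph uses sex as a factor, stratum or covariate.

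The power calculation assumes "a standard deviation of 0.001 for the CSF-to-plasma ratio" and states that "studying 17 individuals in each genotype group will allow us to detect" with "80% power and an alpha of 0.05 a difference of 0.001 between" the two genotype groups. Three more participants per group are enrolled because some are expected not to be evaluable.

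**The concern.** Sex is held fixed by design, so an analysis that respects the design would use it. With equal sex splits, a sex difference cancels out of the genotype difference but stays in the pooled SD on which the t test relies. The standard error then overstates the uncertainty of the estimate: intervals are too wide, the type I error falls below its nominal level, and power is lost that the balanced enrolment has already made available.

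Balance at analysis is also not assured. The protocol allows for three non-evaluable participants per group, takes non-adherent participants off study (section 6.0.3), and permits withdrawal when CSF cannot be obtained (Study Withdrawal/Discontinuation). Nothing keeps the evaluable set at equal numbers of men and women, and an unadjusted test does not correct for a difference between the groups in sex mix.

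Each participant has a lumbar puncture, and the protocol calls its own power calculation rough, so precision that can be had from data already in hand is worth taking.

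**Working it through.** **Inputs from the protocol.** Difference 0.001 and SD 0.001 (a 1-SD effect), alpha 0.05 (two-sided reproduces the stated number), 17 evaluable per group, 20 enrolled per group in cells of 10.

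**Input not in the protocol.** The effect of sex on the ratio. I take sex to explain a share f of the variance within a genotype group, with f = 5%, 10%, 20% or 30%. The sex difference in within-cell SDs is d = 2√(f/(1−f)), that is 0.46, 0.67, 1.00 and 1.31.

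**1. The plan's own figure.** Noncentral t with noncentrality 1/√(2/n) gives power 78.1% at n = 16 and 80.7% at n = 17. The stated 17 is right.

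**2. Power with sex in the model.** The residual SD becomes √(1−f), with 34 − 3 = 31 df. The noncentrality is 1/(√(1−f) × √(2/17)) = 2.915/√(1−f). For f = 20% this is 2.915/0.894 = 3.26, giving 88.4%.

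**3. Width of the unadjusted interval relative to the adjusted one.** With 9/8 in both groups, the within-group sum of squares of the sex indicator is S = 2 × 9 × 8/17 = 8.47. The ratio is √(1 + S d²/32) × t(32 df)/t(31 df). For f = 20%, d² = 1, so √(1 + 8.47/32) = 1.125, and 1.125 × 2.0369/2.0395 = 1.123. Four full cells of 10 give √(1 + 10/38) = 1.124 before the same small correction, which is practically identical.

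**4. Unadjusted power and type I error.** These were simulated with 9/8 in both groups.

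| Share of variance due to sex | Power, unadjusted | Power, adjusted | Unadjusted interval too wide by | Type I error, unadjusted |
|---|---|---|---|---|
| 5% | about 81% | 82.6% | 3% | about 4.5% |
| 10% | about 82% | 84.5% | 6% | about 4% |
| 20% | about 83% | 88.4% | 12% | about 3% |
| 30% | about 84% | 92.1% | 20% | about 2% |

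The adjusted test stays at about 5%.

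**5. Uneven splits.** The largest opposite imbalance within the allowance of three losses per group is 10/7 in one group and 7/10 in the other. The sex difference in total SDs is 2√f, which is 0.894 at f = 20%. The unadjusted estimate is shifted by (3/17) × 0.894 = 0.16 SD. If that works against the genotype effect, power is about 68% unadjusted and about 88% adjusted. If it works in favour, unadjusted power rises to about 93%. The mild 9/8 against 8/9 split gives about 78% or 87% unadjusted, depending on direction.

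**6. Price if sex has no effect.** With the same split in both groups, 80.7% becomes 80.6%. With 9/8 against 8/9 the loss is about 0.2 points. In the extreme 10/7 against 7/10 split it is about 1.3 points.

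**The case against.** The strongest reply is that the harm depends on an effect the protocol nowhere asserts. It does not say that sex influences raltegravir in plasma or CSF, and it states that the ratio itself cannot be predicted reliably. A sex share of 30% means a difference of 1.3 within-cell SD, which is large. At 0.25 SD the interval is less than 1% too wide. This stands: the size of the gain is unknown and could be trivial.

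A second reply is that the error is on the safe side. This also stands. A reader might infer that the primary test is invalid or raises the false-positive rate. Under balance the estimate is unbiased and the type I error is at or below 5%. A reader might also infer that the trial falls short of its 80% power. Taking 0.001 as the SD within a genotype group, as the text reads, unadjusted power under balance is above 80% at every share examined. Values of 78% to 79% arise only when a small sex imbalance happens to oppose the genotype effect, and the mirror-image imbalance raises power instead. Nor are the quotas wasted: they still protect the genotype contrast from confounding by sex.

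A third reply is that covariate adjustment belongs in a statistical analysis plan, which is not shown. That holds only in part, because the protocol itself names the two-group test. Its wording on the nonparametric route is open enough to admit a stratified version, but does not call for one.

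**Conclusion.** The point holds as an efficiency improvement. The stated analysis omits the factor on which enrolment is balanced. If sex explains 5% to 30% of the variance, this leaves intervals about 3% to 20% too wide and gives up roughly 1 to 8 points of power under balance. It also leaves any sex imbalance among evaluable participants uncorrected, which could matter more: about 68% against 88% power in the adverse extreme at a 20% share.

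These sizes rest on an assumed sex effect, a sex difference that is the same in both genotypes, normal data and an SD of 0.001 across both sexes. If 0.001 was meant as the SD within one sex, the unadjusted test does less well than the plan implies: with four full cells of 10 and a sex difference of 1 SD, power is 81% unadjusted against 87% adjusted. The documents support no claim of invalidity or excess false positives.

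**What to change.** In the Statistical analyses paragraph, replace the t test with a linear model for each primary ratio, transformed if needed, with genotype and sex as factors, and report the genotype effect with its 95% confidence interval. Keep a rank-based route for non-normal data as the stated fallback, but replace the unstratified Mann-Whitney test with its sex-stratified (van Elteren) version.

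This takes one or two sentences. Sex is already recorded, and neither enrolment nor data collection changes. The cost is one degree of freedom, about 0.2 points of power at most under near-balance if sex turns out not to matter.
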